#### Virtual reality one-session therapy

VR OST was designed as a serious game [23] with game progression entailing gradually increased stimuli intensity. The application consists of a number of zones, each containing three types of gamified tasks for the user to complete: (1) looking at spiders, (2) interacting with spiders to complete rudimentary game mechanics, and (3) a task where the user is approached by a spider. With completion of tasks and progression through the zones, spider stimuli become increasingly more intense, from a cute, cartoonish spider through realistically depicted tarantulas. See Fig. 2 for a screenshot from the application. Two virtual environments will be used: a living room environment and an outdoor suburban backyard environment. User input is strictly gaze-derived and is used for the interactive game mechanics, reporting SUD and more. Once initiated, the application is fully automated (i.e., no therapist action required) and includes a system for saving and compiling SUD and other input, a virtual therapist providing instructions through voiceover, support and summaries of progress, and information about spiders. Unlike the OST treatment, participants in the VR condition will be seated throughout the duration of therapy, but both groups will be time-limited to 3-h duration. Although the VR treatment is automated, a clinical psychologist will be in attendance (one-to-one) with the participant in case of technical or other difficulties.

**Fig. 2 Fig2:**
[figure not shown]
Screenshot from the virtual reality application

In this study, the Samsung Gear VR platform (powered by a Samsung Galaxy Note 4 or Galaxy S6, both running Android 5.0) will be used to create the VR environment. Availability of the VR application on other VR platforms (e.g., Oculus and Vive) is planned.

### Analyses

Data will be analyzed on an intention-to-treat basis, using mixed effects models [48]. This trial was powered to detect a non-inferiority margin of a 2-point between-group difference, with a standard deviation of 4. The margin and standard deviation were based on previous research on traditional OST [36]. In accordance with the non-inferiority design, we hypothesize that the lower bound of the 95 % confidence interval of the between-group difference will not be larger than 2. On the basis of these parameters (and 80 % power), the study will require 50 participants assigned to each group (*N* = 100 total). In addition to the non-inferiority analyses, standard mixed models will be used to investigate effects of time and group on primary and secondary outcome measures. Within- and between-group effect sizes will be calculated using Cohen’s *d*. The influence on outcomes of demographic and other non-clinical variables (e.g., experience with gaming) will also be examined. All design, implementation, and reporting will be carried out in accordance with CONSORT and SPIRIT guidelines [49–51].

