### Measures

#### Primary outcome measure

Change from baseline on the BAT will serve as the primary outcome measure. To study the real-world effects of VR therapy, all participants will complete the same BAT featuring a real spider. The BAT [35] will feature 13 steps (scored 0–12) corresponding to sequentially closer contact with the spider. See Table 1 for sequence details. The BAT will begin with participants standing outside a room (approximately 3 × 5 m large) where there will be a table placed farthest away from the door, on which a transparent container (about 40 × 30 × 19 cm large) will house the spider (medium-sized; see below). The participants will be informed that the objective of the exercise is to pick up and hold the spider in their hands for 20 seconds. They will be encouraged to do their best but will be told that they can abort the exercise at any time. A pretreatment score of 9 or less [36] will be required for study inclusion.

**Table 1 Tab1:** Behavioral Approach Test step specifications

Score	Details
0	Refusal to enter room
1	Enters room but stops before covering one-fifth of the distance to the container
2	Stops before covering two-fifths of the distance to the container
3	Stops before covering three-fifths of the distance to the container
4	Stops before covering four-fifths of the distance to the container
5	Stops before covering all of the distance to the container
6	Reaches the table with the container
7	Touches the container
8	Removes the lid of the container
9	Puts a hand inside the container
10	Touches the spider with at least one finger
11	Holds spider in hands for less than 20 seconds
12	Holds spider in hands for 20 seconds or more

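### The non-inferiority criterion gives no order of subtraction and, as worded, does not test the 2-point margin in either direction

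*Protocol article*

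**What the plan says.** The criterion is in the Analyses section of the protocol article. It is given as a hypothesis that follows from the non-inferiority design: "we hypothesize that the lower bound of the 95 % confidence interval" of the group difference, with the condition that this "confidence interval of the between-group difference will not be larger than 2".

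The same section gives the design inputs: "This trial was powered to detect a non-inferiority margin of a 2-point between-group difference", "with a standard deviation of 4", 80% power, and "the study will require 50 participants assigned to each group". The margin has no sign.

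Under Primary outcome measure, the article states that "Change from baseline on the BAT will serve as the primary outcome measure". The scale is "scored 0–12) corresponding to sequentially closer contact with the spider", so a higher score, and a larger gain, is better.

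The Background names the aim as non-inferiority of VR to traditional OST. The order of subtraction is not stated anywhere, and no other section restates or corrects the rule.

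**The concern.** A non-inferiority claim needs the interval to exclude a deficit as large as the margin. The limit on the side unfavourable to VR must therefore be compared with the margin.

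- **OST minus VR** (positive means VR is worse): the upper limit must lie below +2. The written rule uses the lower limit, so it asks only that VR has not been shown to be worse by more than 2 points.
- **VR minus OST** (negative means VR is worse): the lower limit is the right one, but it must lie above -2. The written rule asks for it to be at or below +2, which can fail only when VR is clearly better.

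This sentence is the only place where the article ties the margin to a confidence interval. If it is followed as written, the false non-inferiority rate is not controlled. The article also promises public release of the dataset and analysis scripts, so outside readers will compare the reported conclusion with this sentence.

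**Working it through.** **Inputs** (Analyses section): margin 2, SD 4, 50 per arm, 80% power. Direction of benefit: higher is better (Primary outcome measure). Assumptions: normal approximation, no dropout, and no gain in precision from baseline or repeated measures.

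**1. The plan's sample size, with true difference 0.**
n per arm = 2 × SD² × (z_alpha + z_power)² / margin² = 8 × (z_alpha + 0.842)²
- One-sided 5%: 8 × (1.645 + 0.842)² = 49.5, rounded up to 50. This is the stated figure.
- One-sided 2.5% (the limit of a two-sided 95% interval): 8 × (1.960 + 0.842)² = 62.8, rounded up to 63. This is not the stated figure.

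**2. Precision at 50 per arm.**
SE = 4 × √(2/50) = 0.80. The two-sided 95% half-width is 1.96 × 0.80 = 1.57.

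**3. Observed results that pass.**
- Literal rule, OST minus VR: estimate - 1.57 ≤ 2, so any observed VR deficit up to 3.57 points passes.
- Literal rule, VR minus OST: every observed VR deficit passes; the rule fails only if VR is better by more than 3.57 points.
- Correct rule, either scale: the observed VR deficit must be below 2 - 1.57 = 0.43 points.

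Example: OST minus VR = 3.0 has a 95% interval of 3.0 ± 1.57, or 1.4 to 4.6. The interval excludes zero and the estimate exceeds the margin, yet the lower bound of 1.4 satisfies the written rule.

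**4. Probability of declaring non-inferiority when VR is truly worse by d points.**
- Literal, OST minus VR: Φ((2 + 1.57 - d)/0.80)
- Literal, VR minus OST: Φ((2 + 1.57 + d)/0.80)
- Correct: Φ((2 - 1.57 - d)/0.80)

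| True VR deficit d | Literal, OST minus VR | Literal, VR minus OST | Correct rule |
|---|---|---|---|
| 2 | 97.5% | about 100% | 2.5% |
| 3 | 76% | about 100% | 0.07% |
| 4 | 29% | about 100% | about 0% |

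**5. The same check with a one-sided 95% limit.**
The half-width is 1.645 × 0.80 = 1.32. At d = 2 the literal rule passes 95% (OST minus VR) or about 100% (VR minus OST), and the correct rule passes 5%. The problem does not depend on which confidence level was meant.

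**6. Power of the correct rule when the arms are equal.**
- One-sided 95% limit: Φ(2/0.80 - 1.645) = Φ(0.855) = 80.4%.
- Limit of a two-sided 95% interval: Φ(2/0.80 - 1.960) = Φ(0.540) = 70.5%.

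**The case against.** The strongest reply is that the intended meaning is plain. The section treats the margin as an unsigned size. If the criterion is read the same way, it says that the VR deficit at the unfavourable limit is no more than 2 points, which is a correct rule. The sample size supports this, because 50 per arm follows from a proper one-sided 5% non-inferiority test. The sentence is also phrased as a hypothesis in a condensed article.

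Much of this stands as a statement about intent. It does not rescue the text: the reader must supply both the order of subtraction and an absolute value, and neither is written. Nor is this detail left to an analysis plan, since the criterion is stated and is wrong as stated.

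Three stronger readings are tempting, and the documents do not support them.
- A reader might infer that the plan simply picked the wrong confidence limit. That is so only for OST minus VR. For VR minus OST the lower limit is right, and changing it to the upper limit would create a new error.
- A reader might infer that almost any result would pass. For OST minus VR that is too strong: at a true 4-point deficit the literal rule passes 29% of the time.
- A reader might infer that the trial will make false claims at these rates. The percentages describe the literal wording. Nothing shows that the sponsor would analyse the data that way, and the VR minus OST version is so implausible that it is unlikely anyone intended it.

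**Conclusion.** The point holds as a mis-specified criterion. The order of subtraction is missing, and the written condition protects the 2-point margin on neither scale. At a true 2-point VR deficit the literal rule would pass 97.5% or about 100% of the time, against 2.5% for a correct rule based on a two-sided 95% interval. These figures rest on the plan's SD of 4, 50 analysed per arm and the normal approximation. A different SE changes the figures at larger deficits but not the 97.5% at the margin.

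The intended test was probably sound, so this is a fault of specification and not evidence of a flawed design. It still needs correcting before analysis, because it is the only stated criterion for the primary claim.

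A linked ambiguity should be settled in the same sentence. The article refers to a 95% interval without saying whether it is one-sided or two-sided. The stated 80% power at 50 per arm matches only the one-sided version.

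**What to change.** Replace the criterion with one sentence that fixes order, sign and limit together, for example: *The difference is VR minus OST in BAT change from baseline (positive favours VR); non-inferiority is concluded if the lower 95% confidence limit is above -2 points.* Equivalently, the upper limit of OST minus VR must be below +2. Replacing the word lower with upper, without stating the order, is not enough.

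In the same place, state which 95% limit is meant:
- **One-sided 95%:** the false-claim rate at the margin is 5%. Power is about 80% at 50 per arm, so the stated sample size stands.
- **Two-sided 95% interval:** the false-claim rate at the margin is 2.5%. Power at 50 per arm should be restated as about 70%. Keeping 80% would need 63 per arm, or 2 × 63 = 126 in total, which is 26 more than planned.

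Correcting the direction costs one sentence and no extra participants or data. Only the choice of a two-sided interval carries a further cost, in power or in sample size.

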### Procedure

To recruit a diverse sample, multiple recruitment methods will be used, primarily postings in online forums and through coverage in national television, newspapers, and magazines [32]. Potential participants will be directed to the study website (www.vimse.se), where they will find more information about the study and can complete the online screening battery. Participants meeting inclusion criteria will travel to Stockholm University to complete the premeasurement, including self-rating scales, a diagnostic interview, and a Behavioral Approach Test (BAT). If suitable for inclusion, participants will be randomized and, approximately 1 week after the premeasurement occasion, will complete the allocated treatment session. Posttreatment measurements will take place approximately 1 week after the treatment session. Additional follow-up measurements are planned after 12 and 52 weeks. See Fig. 1 for the study flowchart.

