**Fig. 1 Fig1:**
[figure not shown]
Study flowchart. *BAT* Behavioral Approach Test

Subjects will be randomized to treatment arms (using a true random number generator: www.random.org) after completing the premeasurement in preset blocks of 4, 6, 8, or 10 (randomly sized) with even group allocation in each block. Randomization will be performed by a research assistant not otherwise involved in the study, and allocation will be blinded to all but the treatment coordinator and the assigned therapist. As in most psychological research, blinding participants to treatment allocation is not feasible. For ethical reasons, subjects are informed at premeasurement of the two possible treatment allocations, and their preference (and strength thereof) is noted to enable investigation of mediating effects of treatment preference. The therapist administering the posttreatment assessment will be blinded to treatment allocation until all outcome measures have been completed.

All data gathered during the study will be stored anonymously. No contractual agreements limit access by other investigators to this data or to final datasets, and upon completion the dataset generated in this trial will be published in a data repository (e.g., Dryad or figshare), accompanied by the script files to reproduce the statistical analyses.

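### Fifty per group gives the stated 80% power only at one-sided 5% (a 90% interval); under the stated 95% confidence interval power is about 70%, and lower with any loss of outcome data

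*Protocol article*

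**What the plan says.** The whole sample-size statement is in the Analyses section of the protocol article. It gives the margin and variability together: "This trial was powered to detect a non-inferiority margin of a 2-point between-group difference, with a standard deviation of 4". The decision rule follows, in the hypothesis that "the lower bound of the 95 % confidence interval of the between-group difference will not be larger than 2". The next sentence derives the size from those inputs plus 80% power: "the study will require 50 participants assigned to each group", 100 in total.

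The section gives no significance level or sidedness other than the 95% interval. It states no assumed true difference and no allowance for loss. The Abstract and the Sample section use the same 100 as the number to be enrolled, so the number required and the number randomized are identical. The first post-treatment assessment is about 1 week after the session, and the Procedure section adds: "Additional follow-up measurements are planned after 12 and 52 weeks".

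**The concern.** The confidence level of the decision interval fixes the type I error of a non-inferiority test. Comparing one bound of a two-sided 95% interval with the margin is a test at one-sided 2.5%. A sample size presented as following from that rule should therefore use 2.5%, and 50 per group looks too small for it.

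Two things are at stake. First, if the 95% interval governs, the trial's main question has a materially higher chance of an inconclusive answer than the article states. Second, the sample size and the decision rule imply different type I error levels for the primary claim, so the article can be read as supporting either a 95% or a 90% interval. Some results would pass one and fail the other.

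**Working it through.** **Inputs.** Margin M = 2, SD = 4, power 80% and the 95% interval all come from the Analyses section. Allocation is 1:1, because randomization is in blocks "with even group allocation in each block" (Procedure section, after the flowchart). The true difference is taken as 0; this is my assumption. I read the rule as comparing the bound on the side unfavourable to VR with the margin.

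**Formula.** n per group = 2 × (z_α + z_β)² × SD² / M², with z_β = 0.842 for 80% power.

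**Reproducing the article's figure.**
- One-sided 5% (z_α = 1.645): 2 × (1.645 + 0.842)² × 16/4 = 49.5, so **50 per group**. This matches.

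**With the stated 95% interval.**
- One-sided 2.5% (z_α = 1.960): 2 × (1.960 + 0.842)² × 16/4 = 62.8, so **63 per group**, 126 in total. This does not match.
- The t-based equivalents are 51 and 64 per group, so the gap is not a matter of approximation.

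**Power at 50 per group.** The standard error of the difference is 4 × √(2/50) = 0.8, and M/SE = 2/0.8 = 2.5.
- One-sided 5%: Φ(2.5 − 1.645) = 80.4% (t-based 79.9%).
- One-sided 2.5%: Φ(2.5 − 1.960) = Φ(0.54) = **70.5%** (t-based 69.7%).

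**What would restore 80% at 50 per group with the 95% interval**, changing one input at a time:
- SD: 2 / (0.2 × 2.802) = 3.57 instead of 4.
- Margin: 0.8 × 2.802 = 2.24 instead of 2.
- True difference: 2.24 − 2 = 0.24 points in favour of VR instead of 0.

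**Where the two readings part.** The half-widths are 1.960 × 0.8 = 1.57 for the 95% interval and 1.645 × 0.8 = 1.32 for the 90% interval. Non-inferiority is shown if the observed deficit is below 2 − 1.57 = 0.43 points under the first, or below 2 − 1.32 = 0.68 points under the second. An observed deficit between about 0.43 and 0.68 points passes one and fails the other.

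**Loss of outcome data.** The article gives no rate, so these are assumed values, and each lost participant is treated as contributing nothing.

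| Assumed loss | Evaluable per group | Power, 95% interval | Power, 90% interval |
|---|---|---|---|
| 0% | 50 | 70.5% | 80.4% |
| 10% | 45 | 66.0% | 76.6% |
| 20% | 40 | 60.9% | 72.3% |

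**The case against.** **A one-sided bound may have been meant.** The article never says two-sided and compares only one bound with the margin. A one-sided 95% bound is a one-sided 5% test, and 50 per group would then be right. This is a plausible explanation of where the number came from. But an unqualified 95% confidence interval is ordinarily read as two-sided, so under this reading too the text needs correcting.

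**The 70% may not be the power of the planned analysis.** The primary outcome is change from baseline and the analysis is a mixed model, whereas the calculation is an unadjusted two-group comparison. The SD of 4 comes from a cited study and could describe a post-treatment score, a change or a residual. If it is an unadjusted post-treatment SD, adjustment for a baseline correlated at about 0.45 would bring the effective SD to 3.57 and restore 80%. That limits how firmly 70% can be attached to the final analysis. It does not rescue the statement, because the article claims no such gain and derives 50 directly from the SD of 4.

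**Loss to follow-up is a detail a condensed article may omit.** This is fair, and the point does not depend on it. Loss at week 52 would not reduce the number assessed 1 week after treatment, and a mixed model keeps partial data, so the table shows the effect of missing outcomes at the time point being tested. What stands is that the 50 assigned equal the bare formula result, so they contain no allowance.

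**The consequence is limited.** Under the two-sided 95% reading, type I error is controlled at 2.5%, so the risk is an inconclusive trial, not a false claim of non-inferiority. That is true, but it does not make the stated power correct or settle which level governs.

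**Conclusion.** The point holds. The sample size uses one-sided 5%, while the decision rule, read in the ordinary way, uses one-sided 2.5%. Under the article's own interval, 50 per group gives about 70% power, not 80%. The shortfall against the 63 required is 13 per group, or 26 participants. This rests on a margin of 2, an SD of 4 for the analysed quantity, a true difference of 0 and complete data. The first two are the article's figures, except that it does not say which quantity the SD describes; the last two are assumptions. Missing outcomes lower power further, to about 66% or 61% at assumed losses of 10% or 20%.

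**What to change.** Preferred: keep N = 100 and the two-sided 95% interval, and restate power as about 70% with complete data for margin 2, SD 4 and true difference 0, adding about 66% and 61% as illustrations at assumed losses of 10% and 20%.

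Alternative: if one-sided 5% was intended, say so explicitly and change the decision interval to a two-sided 90% interval, which is the same test as a one-sided 95% bound. Power is then 80.4% with complete data.

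In either case, state that the SD of 4 is the SD of the quantity analysed, or say what it describes. If the primary model adjusts for baseline and the sponsor relies on that to recover power, state the correlation assumed and the resulting power.

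The cost is a few sentences and, under the preferred option, a less favourable power figure. No extra participants are needed. The Trial status section reports recruitment already under way at submission, so the choice should be recorded before outcome data are examined.

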## Discussion

The aim of this study is to evaluate the effectiveness of VR exposure therapy compared with traditional one-session exposure therapy using a randomized controlled design and subjects diagnosed with spider phobia. The introduction of modern VR headsets combined with powerful but relatively inexpensive computers capable of displaying realistic stimuli, in addition to the historical lack of high-quality randomized controlled trials [52], suggest that this is an opportune time to make use of this rapidly advancing technology and translate it into clinically validated mental health treatments. VR exposure therapy has already been theoretically and empirically evaluated to be well-suited for the treatment of specific phobias [53]. The authors of a recent meta-analysis [54] provided additional evidence based on behavioral assessment rather than self-report of internal states. VR exposure-treated subjects, in their review of 14 studies, improved significantly after treatment (*g* = 1.23) and compared with control subjects (*g* = 1.41). No significant differences were identified after treatment and in follow-up between in vivo and VR exposures.

Conducting VR exposure therapy using modern, commercially available VR equipment may prove even more powerful. In addition to the evaluation of modern VR hardware, our intent in this study is also to evaluate a newly developed, gamified exposure application for the treatment of specific phobias. The software includes advancements such as multiple open-ended exposure scenarios relying on gamification to improve engagement and interest; multiple stimulus intensity variables such as appearance (small to large spiders, cartoon-like to hairy), behavior (more or less predictable, static, and aggressive), a variable number of spiders, and changes in lighting and protective barriers (such as caged or not); a virtual therapist that guides the participant in the use of the application and provides psychoeducation and expert advice about spiders; and inclusion of a gaze direction trackpad to allow participants to interact with the stimuli.

Recent evidence indicates that treatment benefits of exposure therapy accrue as a result of new inhibitory learning and not habituation of the conditioned response to phobic stimuli [55]. Physiological habituation (viz., reduced heart rate and galvanic skin response) may serve as a safety signal alleviating fear in the short term but inhibiting long-term learning and extinction [56]. Serious game treatments in which there is a sense of play, interactivity, flow, and creative solutions have the potential to promote new learning [57]. In an exposure therapy context, these should create engagement (rather than avoidance) by producing a mismatch between expectancy and outcome and require flexible responding [55]. In a study in which a fear of heights group received random levels of exposure intensity and approached stimuli in multiple ways versus a steady intensity increase group, researchers found improved fear reduction in the former, without a need for physiological habituation [58].

Limitations of the present study include an exposure application that involves multiple unique design specifications, making disentangling of specific therapeutic factors difficult. Despite the complete automation of the VR application, psychologists will be in attendance to resolve technical difficulties and ensure treatment compliance and will be present to assist patients if needed. Future studies will benefit from having the patient administer VR treatment independently to ensure true isolation of treatment effects. In addition, physiological monitoring of subjects will not be possible during this study but may prove helpful in interpreting the results of future studies.

In sum, spider phobia is a common disorder [1] that has a negative impact on life, work, and leisure activities [6] but goes largely untreated [3]. VR exposure therapy may provide improvements in efficacy [15], access, standardization of protocols, and cost-effectiveness [31]. Although not evaluated in this study, virtual OST also has the potential to conveniently continue maintenance therapy once regular treatment has been completed. This study is, to our knowledge, the first to test the efficacy of a modern, market-ready VR application for the treatment of spider phobia, and it will assist in the development of a new method for the delivery of evidence-based treatments.

